## Abstract

**Background:**

Oral microbiome transplantation (OMT) is a novel concept of introducing health-associated oral microbiota into the oral cavity of a diseased patient. The premise is to reverse the state of oral dysbiosis, and restore the ecological balance to maintain a stable homeostasis with the host immune system. This study will assess the effectiveness, feasibility, and safety of OMT using an interdisciplinary approach.

**Methods/Design:**

To find donors suitable for microbial transplantation, supragingival plaque samples will be collected from 600 healthy participants. Each sample (200μL) will subsequently be examined in two ways: 1) 100μL of the sample will undergo high-throughput 16S rRNA gene amplicon sequencing and shotgun sequencing to identify the composition and characterisation of a healthy supragingival microbiome, 2) the remaining 100μL of the plaque sample will be mixed with 25% artificial saliva medium and inoculated into a specialised *in-vitro* flow cell model containing a hydroxyapatite disk. To obtain sufficient donor plaque, the samples would be grown for 14 days and further analysed microscopically and sequenced to examine and confirm the growth and survival of the microbiota. Samples with the healthiest microbiota would then be incorporated in a hydrogel delivery vehicle to enable transplantation of the donor oral microbiota. The third step would be to test the effectiveness of OMT in caries and periodontitis animal models for efficacy and safety for the treatment of oral diseases.

**Discussion:**

If OMTs are found to be successful, it can form a new treatment method for common oral diseases such as dental caries and periodontitis. OMTs may have the potential to modulate the oral microbiota and shift the ecological imbalances to a healthier state.

## Background

### Microbiota are essential for human physiology and health

The human body has co-evolved with approximately a trillion microbes that inhabit different niches and create an adaptive ecosystem that can influence host physiology [1]. The microorganisms in the body, collectively called microbiota, contribute to 200 grams of total body weight of an average person weighing 70 kg [2]. Microbiota inside and outside the body are estimated to outnumber human somatic and germ cells, suggesting that we reframe the human body as a ‘superorganism’–an aggregation of the human body and the microbiome as one [3]. Microbiota contribute to host health by modulating the immune system, maintaining homeostasis, and defending against infection.

### Oral microbiome in dental caries and periodontal disease

The oral cavity harbours the second most complex microbial community in the body, followed by the colon [4]. The oral microbiome–the microorganisms and their environmental context–consists of 484 out of 775 bacterial taxa that are exclusively found in the oral cavity, according to the expanded Human Oral Microbiome Database (eHOMD) [5]. The tooth surface is the only non-shedding surface in the oral cavity compared to other areas in the mouth, and this facilitates a stable anchoring environment for growth and development of the microbiota. The supragingival and subgingival microbiomes are two of these key ecosystems and are comprised of diverse biofilms, but differ substantially in composition. The supragingival microbiome is demarcated by bacteria, such as *Streptococcus*, *Actinomyces*, *Haemophilus*, *Neisseria*, *Veillonella*, *Fusobacterium*, *Oribacterium*, and *Rothia* [6, 7], while the subgingival microbiome is predominated by *Treponema denticola*, *Tannerella forsythia*, *Aggregatibacter actinomycetemcomitans*, *Fretibacterium*, *Porphyromonas*, *Peptococcus*, *Filifactor*, and *Mycoplasma* [8].

Dysbiosis is a term utilized to describe a perturbation in the microbiome that departs from an otherwise balanced ecology to prolong, exacerbate, or induce detrimental health [1]. While the use of the term can by problematic [9] dysbiosis in the oral microbiome is described in numerous health conditions, notably dental caries and periodontal disease. Typically, dental caries is linked to dysbiosis of the supragingival microbiome, while subgingival microbiome dysbiosis may lead to periodontal disease [7, 10], although dysbiosis in other oral microbiotas (such as saliva) have also been linked to these oral diseases [11].

Dental caries is a dynamic, microbial biofilm-mediated, multifactorial, sucrose-driven disease that results from an unbalance in a phasic demineralization and remineralisation, which can subsequently cause demineralization of hard dental tissues [12]. Cariogenic bacteria colonizing the oral cavity are influenced by diet [13], as frequent intake of carbohydrate (mainly sucrose) can disrupt the ecology of this community by the selection of acidogenic and acid tolerant species that are responsible for caries development [12]. Previous research suggested that the primary pathogen for dental caries in children and adults was *Streptococcus mutans* [14]. While this pathogen certainly contributes to caries formation in some people, recent advances in High Throughput Sequencing (HTS) of the 16S ribosomal RNA encoding gene have identified additional microbes linked to shifts in non-mutans streptococci, such as *Streptococcus sanguinis*, *Streptococcus oralis*, and *Streptococcus mitis*, as the initial colonizers [7, 15], as well as *Lactobacilli*, *Actinomyces*, *Bifidobacteria*, and yeast species [7].

Periodontal disease is a multifactorial, polymicrobial disease resulting in periodontal pocket formation, clinical attachment loss, bone loss, and subsequent leading to loss of tooth structure. In the transition from health to periodontal disease, there is an emergence of low abundant species and increased species diversity [10]. According to Socransky’s model, the bacteria associated with periodontal disease belong to the so-called red complex, comprising *P*. *gingivalis*, *Tannerella forsythia*, and *Treponema denticola* [16]. However, as with dental caries, additional organisms have been identified using HTS. Bacteria associated with periodontitis are now considered to include distinct phyla (*Spirochetes* and *Bacteroidetes*), genera (*Treponema*, *Synergistes*, *Prevotella*, *Synergistes*, *Megaspaera*, *Selenomonas* and *Desulfobulbus*), and previously uncultivable species, including Gram-positive *Filifactor alocis* and *Peptostreptococcus stomatis* [17].

### Conventional treatment of oral diseases

Conventional methods for both the treatment dental caries and periodontal disease involves causative therapy. The treatment of dental caries involves removal of demineralised tissue and replacing with filling material [12]. The primary treatment for periodontal disease is mechanical removal of the plaque biofilm and management of the potential risk factors (for example, better glycaemic control in diabetic patients or reduction in smoking for active tobacco smokers). Although current methods are effective in managing dental caries and periodontal disease, they fall short of completely preventing and arresting the diseases before they occur, resulting in potential short term benefits and the likely re-emergence of disease [18]. The failure rates of dental restorative materials are high, at an annual rate of 8% due to secondary caries and bulk fracture [19]. Earlier interventional options, such as application of resin-based sealants on permanent molars, reduce caries by only 11%-51% [20] for limited time period of up to 48 months [21]. In the case of periodontal disease, almost all on periodontal maintenance therapy continue to show signs of progressive clinical attachment loss, with one to two thirds of people losing at least one tooth during an extended period of periodontal maintenance care [22]. It is clearly imperative to find necessary ways for better preventing and managing periodontitis and dental caries. This is especially true considering higher rates of tooth loss in ageing populations [23] and severe caries rates of disease in young children [24]. Oral microbiome therapy (OMT) may offer an effective alternative for the treatment of common oral diseases.

### Developing oral microbiome transplantation therapy in Australia

Oral microbiome transplantation (OMT) is a similar concept to Faecal Microbiome Transplant, which involves transferring oral bacteria from a healthy donor to a patient suffering from a disease, such as dental caries or periodontitis. OMT therapy has recently been successfully performed among dogs with naturally occurring periodontitis [25]; this successful procedure in canines involved placing healthy donor plaque samples into a sterile saline solution, loading the mixture on a nylon swab, and swabbing/irrigating the tooth surface of the transplant recipient. While this procedure has been proposed in humans using an array of techniques [26, 27], this procedure has not yet been completed in humans, and the most appropriate, effective approach has not yet been identified. Direct transplantation in humans from a donor to recipient requires logistic considerations and may require the identity of the donor and recipient to be revealed to one another. It is also unclear if the irrigation method could deliver enough microorganisms for a successful OMT transfer.

To overcome this, we propose a novel approach to developing and testing OMT prior to human clinical trials. Overall, our approach involves (1) identifying and scrutinizing healthy donor plaque material; (2) growing the plaque microbiota *in vitro* in a flow cell, developed by extending the work of several previous teams [25, 26, 28, 29]; (3) integrating donor oral microbiota into a formulated hydrogel; and (4) transplanting donor material into an animal model of oral disease to test its efficacy and safety.

A key aspect of this study is the identification of healthy donors. The microbiome of a ‘healthy’ person shows a large degree of interpersonal diversity and finding a single ‘healthy’ state across all individuals is unlikely [10], making donor identification a complex process. However, concept of a ‘super donor’ is derived from faecal microbiome transplantation [30] and describes faecal donor material that results in significantly more successful outcomes than the stools of other donors; for example, the super-donor effect has been observed in various clinical trials for the treatment of inflammatory bowel disease [31, 32]. In the gut, ‘super donor’ microbiota is largely associated with the presence of keystone species or high diversity–features that are not necessarily linked to health improvements in the mouth (e.g., keystone species, such as *P*.*gingivalis* can be considered an oral pathogen [33, 34] and a higher diversity in oral microbiota can be linked with disease, such as periodontal disease [34]). In canine OMT, the authors confirmed that the oral microbiome of healthy dogs/participant was different from the oral microbiome of both periodontitis [25, 27] and edentulous patients [27] but failed to identify the constituents that demarcate a ‘healthy donor’. Therefore, we propose that microbiota from an OMT super donor should have the following characteristics: (1) possesses limited abundances of ‘red’ complex microbes, as defined by Socransky, et al. [16] and known cariogenic species (*e*.*g*., *Streptococcus mutans*) [35]; (2) has no transmissible or infectious pathogens (herpes virus, human immunodeficiency virus, etc.); (3) successfully grow in *in vitro* model, exhibiting higher proportion of live bacterial cells than dead bacterial cells; (4) be able to effectively grow in a host by causing a shift in the microbiome profile of an individual towards that of a donor; and (5) is efficacious against oral disease in a rodent model (*e*.*g*., reduces inflammation) with limited negative outcomes (*e*.*g*., oral infection or increases in oral disease markers). While effective ‘super donors’ need to be further examined during human OMT trials, we hope that these characteristics of donor microbiota will likely improve the chances of OMT success in humans. Nevertheless, additional safety, ethical, and pragmatic considerations need to be examined before OMT therapy is utilized in humans, and this study will provide foundational data necessary to determine if and how human OMT clinical trials should proceed.

## Study aims

The specific aims of the study are as follows:

Aim 1: Describing and identifying the healthy donor and testing the oral biofilm growth using a novel *in vitro* flow cell model.Aim 2: Develop a delivery system for OMT therapy, including hydrogel applications:Aim 3: Test oral microbiota transplant in rodent models:
Examine the safety and efficacy of OMT of human microbiota in healthy rodents.Examine the safety and efficacy of OMT in a rodent caries and periodontal disease model.

## Methods

This study will be conducted in three stages according to each aim (Fig 1).

**Fig 1 pone.0260433.g001:**
[figure not shown]
Study flow diagram.

### Stage 1: Describing and identifying the healthy donor and testing the oral biofilm growth using a novel *in vitro* flow cell model

Supragingival plaque samples will be collected from all healthy participants, as identified during the oral screening process. A part of the samples (100 μl) will be stored at -80 C for downstream cultivation and further sequenced using amplicon and shotgun approaches. The other part (100 μl) of the plaque sample immediately post-collection will be grown *in vitro* on hydroxyapatite discs using a flow cell model for 14 days. The discs would be extracted after 14 days and further assessed microscopically and sequenced through HTS techniques.

### Step 1: Describing the oral plaque microbiome of healthy donors

#### Ethics approval

The study has been approved by the University of Adelaide Human Research Ethics Committee (H-2020-34609) and complied with the Declaration of Helsinki for Medical Research involving Human Subjects. Participation information sheet will be given to each eligible participant (S1 File) and written informed consent will be obtained from participants before their involvement in the study (S2 File).

#### Sample size calculation

It is often challenging to calculate power for microbiome analysis because the true effect size is usually unknown and the relationship between the microbiota community structure and each factor (alpha or beta diversity) is highly dimensional. For our study sample size calculation was based on the methods suggested by Casals-Pascual et al. (2020) [36]. The sample size was calculated using the mean and standard deviation for alpha diversity (species diversity in a community) derived by Burcham et al. (2020) [37]. The minimum expected standard deviation was 2.53. Therefore, at an error of 0.05 and power of 80% the calculated sample size was 583. The sample size was rounded to the nearest 100 to account for loss of samples due to poor sequencing depth.

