#### Study population and recruitment

600 adults aged 18+ years will be recruited. Recruitment will occur in the greater Adelaide region (South Australia) via advertisements in social media and similar platforms. A passive snowballing technique will be used, recruited study participants would be asked to discuss the research project with their family, friends, peers and colleagues and this process will continue until the desired sample size is achieved. The patient interview, clinical and oral assessment, and dental plaque sampling will take place in dental clinics, Adelaide Dental School, University of Adelaide. The recruitment process will begin on June 2021.

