#### DNA extraction and sequencing

DNA from all samples (PBS plaque sample and eight discs) and negative controls will be extracted using a DNeasy PowerSoil Pro Kit®. Amplicon and Shotgun will be employed to: (1) study the overall bacterial population structure and compare communities to existing data sets on healthy individuals (amplicon) and (2) identify specific species and characterize their functions (shotgun).

Amplicon Library analysis: Amplicon sequencing will be done by amplifying the 16S rRNA encoding the V_4_ gene region with region-specific primers, as previously described [44]. Amplicon libraries will then be cleaned, quantified, pooled, and custom sequenced in parallel to a level of >10, 000 sequences per sample on an Illumina MiSeq [44, 45]. The QIIME2 software will be used for analysis of all amplicon data [46]. In QIIME2, amplicon sequence variants (ASVs) will be taxonomically identified by comparisons to eHOMD and the SILVA databases. Alpha diversity (observed species and Shannon’s Diversity Index) and beta-diversity (unweighted UniFrac and Bray-Curtis indices) will be analysed. The donor microbiome will also be compared to healthy supragingival plaque specimens publicly available on QIITA, which is a web-based microbiome comparison platform that allows users to rapidly compare their data with Human Microbiome Project (HMP) and other submitted data sets [47].

Shotgun DNA sequencing library analysis: Shotgun sequencing is random sequencing across entire genomes [48]. To prepare shotgun libraries, custom DNA adaptors with sample specific barcodes will be ligated to random DNA fragments within the samples, as previously described [45]. After cleaning and pooling, shotgun libraries will be sequenced to at least 100 million sequences per sample on an Illumina NovaSeq. To identify bacterial species and functions in the shotgun data, we will map and remove all human sequences and then compare the remaining sequences to a custom curated RefSeq and HOMD genome database and KEGG protein predictions in two analytical pipelines: (1) the MetaPhylan and HUMAnN (2) and the MALT and MEGAN6 CE analysis pipeline packages [45]. This will enable the team to examine links between species and their functions. Bacterial genome assembly using GroopM will be done to link functions to certain species [49].

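### The 80% power at 583 samples names no difference, test or metric, rests on the smallest SD expected, and has only 17 spare samples from rounding as its loss allowance

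*Protocol article*

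**What the plan says.** The section Sample size calculation in the protocol article begins by conceding that in microbiome work "the true effect size is usually unknown". It then says: "The sample size was calculated using the mean and standard deviation for alpha diversity (species diversity in a community"), taken from a cited study and applied with a cited method. The value of that mean is not given. The spread is given: "The minimum expected standard deviation was 2.53". The result follows: "Therefore, at an error of 0.05 and power of 80% the calculated sample size was 583". On loss it says: "The sample size was rounded to the nearest 100 to account for loss of samples due to poor sequencing depth". Study population and recruitment sets the target at 600 adults, described as one cohort.

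Under DNA extraction and sequencing, two alpha-diversity measures are planned: "Alpha diversity (observed species and Shannon’s Diversity Index"). That section also plans to compare the donor samples with existing healthy data sets and with public specimens on QIITA. Neither the measures nor these comparisons are linked to the sample size.

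**The concern.** Power describes a particular test of a particular difference. The section claims 80% and states neither, so a reader cannot tell which Stage 1 result the claim protects.

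Two things the section does state also push the claim in the favourable direction. The required number rises with the square of the SD, so using the smallest SD expected gives the smallest number. Rounding to the nearest 100 is presented as protection against failed sequencing, but its size depends on where the calculated number falls between two hundreds and not on any expected failure rate.

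This paragraph is the article's only justification for recruiting 600 people. A reader would take from it that some Stage 1 comparison has 80% power with sequencing loss already covered. The text supports neither belief.

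**Working it through.** **Inputs from the article.** Error 0.05 and power 80%; SD 2.53, described as the minimum expected; calculated number 583; recruited number 600. Not stated: difference, test, sidedness, groups, metric, value of the mean, loss rate.

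**Assumptions made here.** Normal approximation; two-sided test unless noted (z = 1.960 and 0.842, sum 2.802); SD inflation of 10% to 30%; sequencing loss of 10%.

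**1. Can 583 be reproduced?** Not directly, because the difference is missing. Solving backwards for it:
- One sample: 2.802 × 2.53 / √583 = 0.294 (one-sided 0.261).
- Two equal groups, 583 in total: 2.802 × 2.53 × √(4/583) = 0.587 (one-sided 0.521).

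The article states none of these values. The nearest round differences do not return 583: a one-sample difference of 0.3 needs 559, and a two-group difference of 0.6 needs 560 in total.

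**2. Effect of the SD.** If 583 gives 80% power at SD 2.53, the difference divided by its standard error is 2.802 whatever the difference was. If the true SD is m times larger, power is Φ(2.802/m − 1.960).

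| SD relative to 2.53 | SD | Power at 583 |
|---|---|---|
| ×1.0 | 2.53 | 80% |
| ×1.1 | 2.78 | 72% |
| ×1.2 | 3.04 | 65% |
| ×1.3 | 3.29 | 58% |

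**3. Loss allowance.** 600 − 583 = 17 samples, and 17/600 = 2.8%. With an assumed 10% loss, 600 × 0.9 = 540 remain. Power is then Φ(2.802 × √(540/583) − 1.960) = Φ(0.736), about 77%. Keeping 583 usable at that loss would take 583/0.9 = 648 recruits. If no sample is lost, 600 gives Φ(2.802 × √(600/583) − 1.960) = Φ(0.882), about 81%.

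**4. What the number supports as precision.** The 95% CI half-width for mean alpha diversity is 1.96 × SD/√n.
- SD 2.53: 0.205 at 583; 0.202 at 600; 0.213 at 540.
- At 583 with the SD 20% larger: 0.205 × 1.2 = 0.246. With it 30% larger: 0.205 × 1.3 = 0.267.

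**The case against.** The strongest reply is that nothing here shows an arithmetic error. The article condenses a fuller document, and the calculation relies on a cited method and a cited mean that are not shown. A difference may lie in that mean. This stands: 583 is uncheckable from the article, and that is different from wrong. Sizing on one metric while reporting two is also ordinary practice.

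A second reply is that one cannot say the power belongs to no stated test and also that it drops to 58%. The figures are conditional. Whatever difference lies behind 583, a larger SD at that difference lowers power by the amounts in the table, so the difference need not be known.

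Several stronger readings are tempting but not supported:
- **That Stage 1 contains no comparison.** It plans comparisons with external healthy data sets. What is missing is a link between any of them and the 80%.
- **That 583 is per group, so 1,166 are needed and 600 gives about 52% power.** The article describes no groups, only one cohort.
- **That recruitment by referral breaks independence and shrinks the effective number.** Participants are told of the study by others ("recruited study participants would be asked to discuss the research project with their family, friends, peers and colleagues"), but advertising is used too. The article gives no cluster size or intraclass correlation from which to derive a loss.
- **That 2.8% is too little.** No failure rate is given, so the allowance is unjustified but not shown to be inadequate.

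Finally, Stage 1 is largely descriptive. The donor characteristics listed in the Background include no alpha-diversity test, so no donor selection depends on the 80%. This limits how serious the point is.

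**Conclusion.** The concern holds as a fault in a stated claim and not merely as missing detail. By the section's own description of its SD, 80% is an upper bound at 583 usable samples for whatever difference was used. An SD 10% to 30% above the minimum takes it to between 72% and 58%. The loss allowance is 17 samples (2.8%) left over from rounding, and an assumed 10% loss gives about 77%.

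The SD inflation and the 10% loss are illustrations; neither is in the document. The power figures also assume a two-sided normal-theory test. The 2.8%, and the direction of the SD effect, need no assumption about the missing inputs.

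This should be corrected but is not critical. It is confined to one paragraph, and as a descriptive study the cohort loses little: going from 600 to 540 samples widens the half-width from 0.202 to 0.213, about 5%.

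**What to change.** Rewrite the paragraph in one of two ways.

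1. **Keep a power statement.** Name the comparison, alpha-diversity metric, difference, test and sidedness behind 583. Restate the power for a central or upper SD, at the usable number expected after sequencing loss.
2. **Replace it with precision**, which suits a descriptive stage better. For one named metric, give the 95% CI half-width at SD 2.53 (0.205 at 583, 0.213 at 540), and at 583 for an SD 20% to 30% larger (about 0.25 to 0.27).

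Either way, describe the allowance as the 2.8% it is, or give an expected loss rate with its basis and the usable number that follows.

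The cost is a rewritten paragraph and no additional participants. The drawback is that the stated figure becomes less favourable.
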